#### Data collection

Within the clinical trial, data from three different sources are collected and analysed. In order to be able to combine these different data sources on a case-by-case basis, the operational number of each emergency case is used as a pseudonym. This is deleted when the data sources have been matched.
Rescue Service Case Protocol (‘DIVI-Protocol’).

It is mandatory to document all relevant medical information of any emergency operation served by paramedics in standardised Rescue Service Case Protocols called “DIVI-protocols” (**D**eutsche **I**nterdisziplinäre **V**ereinigung für **I**ntensiv- und Notfallmedizin e.V., the German Interdisciplinary Association for Intensive and Emergency Medicine). We will obtain and analyse extracted and anonymised information of these rescue service protocols of all rescue missions that occur at the four emergency medical service stations during the data collection period (listed in Table 1). These data will allow us a comprehensive overview of the characteristics of rescue operations with both German- and non-German-speaking patients. This is the first investigation of its kind in Germany. We will also compare the quantity and quality of information between patients in the intervention group and in the control groups and match these data with the questionnaires that paramedics are to fill out on emergencies with non-German-speaking patients and data on the usage of the app (see below).

**Table 1 Tab1:** Data on rescue missions obtained from the DIVI-protocols

**Patient demographics**	• Year of birth • Sex
**Emergency Operation**	• Operation site (apartment, retirement home, work place, sports place, doctor’s practice, birth centre, hospital, public space, road, school, educational facility, mass event, other) • Other involved emergency vehicles (NEF*, RTW etc.) • Time of emergency call (hh-mm) • Time of arrival at emergency scene (hh-mm) • Time of arrival at patient (hh-mm) • Time of departure at emergency scene (hh-mm) • Time of arrival at hospital (hh-mm)
**Emergency Case**	• Paramedic’s description of emergency case: event, patient’s medical history, pre-medication (free text) • (Working) diagnosis (free text) • Necessity of ventilation (laryngeal mask, laryngeal tube, endotracheal intubation)
**Medical Aspects**	• Initial Glasgow Coma Scale • Initial NACA-Score • Conditions (stroke, seizure, meningitis, syncope, acute coronary syndrome, STEMI, cardiac arrhythmias, pulmonary embolism, heart failure, orthostatic misregulation, pulmonary edema, cardiogenic shock, pacemaker malfunction, asthma attack, COPD, pneumonia, bronchitis, hyperventilation syndrome, aspiration, haemoptysis, acute abdomen, gastrointestinal bleeding, colic pains, enteritis, psychotic disorders, depression, anxiety, intoxication, suicide (attempt), psychosocial crisis, hypoglycaemia, hyperglycaemia, dehydration, uraemia, fever convulsion, pseudocroup, SIDS, near-SIDS, pregnancy, impending birth, (pre)eclampsia, vaginal bleeding, anaphylactic reaction, heat stroke, hypothermia, frostbite, high fever infection, sepsis, septic infection, influenza, hepatitis / hiv, acute lumbago, epistaxis, social problem (without mental disorder), medical treatment complication) • Injuries (skull & brain, face, neck, thorax, abdomen, spine, pelvis, upper extremities, lower extremities, soft tissues)

*Abbreviations*: **NEF***N**otarzt**e**insatz**f**ahrzeug, i.e. non-transporting emergency physician rapid response car, ***RTW***R**ettungs**t**ransport**w**agen, i.e. patient-transporting ambulance, *NACA* National Advisory Committee for Aeronautics, *STEMI* ST-elevation myocardial infarction, *COPD* chronic obstructive pulmonary disease, *SIDS* sudden infant death syndrome

At the emergency medical service stations in Wendhausen, Königslutter, and Helmstedt, the DIVI-protocols are filled in using a laptop device. The responsible district of Helmstedt will provide us a pseudonymised digital dataset. In Braunschweig the staff uses paper DIVI-protocols that will need to be digitalised. Paper protocols will be scanned and processed with the Optical Character Recognition software Form Pro 3.0 (OCR Systeme GmbH Leipzig, Germany), and will subsequently be reviewed to correct misrecognised values.

For the collection and use of DIVI-protocol-based research data, agreements have been reached with the local authorities of the district of Helmstedt and the City of Braunschweig on the basis of existing laws on the execution of rescue services in Lower Saxony.
b)Questionnaire on emergencies with non-German-speaking patients

The DIVI-protocol by default does not contain any information about communication and mutual understanding. We will therefore introduce a questionnaire to collect these data. Paramedics are asked to fill out questionnaires for all emergencies with patients whose native language presumably is not German. The aim is to determine how often paramedics encounter language barriers, how they experience these emergency operations, and how paramedics’ experience changes when the app is used during the interventional phase. For each rescue mission, the questionnaire can be matched with the corresponding DIVI-protocol. An ambulance is operated by at least two and up to four paramedics, therefore the person who has communicated most with the patient is to complete the questionnaire. The questionnaires should be completed immediately after the operation, but no later than 24 h thereafter. The content of the questionnaire is shown in Additional file 1.
c)Data collected from the mobile device.

Data on paramedics’ use of the app will be collected. This concerns the selected language and e.g. the order of the questions presented to the patient and different types of touch inputs, including ‘missed clicks’ or cancelling. We can then calculate, for example, the time-to-click intervals and average time for completion. This information helps us to understand how paramedics use the app, which questions they ask, and in which order and how they handle the user interface. We can compare the information from the DIVI-Protocols with the use of the app and try to assess the accuracy of the information that is collected through the app. We can also determine the affiliation to a language group of non-German-speaking patients with whom communication is difficult.

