#### Data analysis of the clinical trial

Characteristics of intervention and the two control groups are analysed using descriptive statistics regarding their demografics, medical conditions, assessed communication and native languages (where applicable), and aspects of the emergency operation. Differences between patients of the intervention group and the control groups will be tested for statistical significance using Chi-squared or Mann-Whitney *U*-Tests where applicable. In addition, the groups will be compared according to the recruitment centres in which patients were recruited. Relations between medical aspects of the emergency operation or demographic aspects and the assessed mutual understanding will be analysed using correlation analyses. Changes between control group 2 and the intervention group as to the perceived quality of understanding and to the quantity and quality of obtained information of patients will be analysed using paramedics’ feedback on questionnaires and comparing the content of the free text fields in the DIVI-protocols. In order to enable a comparison between non-German-speaking and German-speaking patients, a control group matched by age, sex, medical condition, and emergency situation will be drawn from the very large group of the German-speaking patients. Then, for example, on-scene times, rates of intubations, and requests for on-scene emergency doctor support can be compared.

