**Fig. 2 Fig2:**
[figure not shown]
Location of the federal state Lower Saxony in Germany (cyan blue) and the study region (encircled in dark blue) (own map)

Lower Saxony has 7.9 million inhabitants and is Germany’s second largest federal state by area. With 167 inhabitants per square kilometre, Lower Saxony is relatively sparsely populated compared to the average in Germany, which is 230 inhabitants per square kilometre, except for the urban sprawl around the capital Hanover and the adjacent city states Hamburg and Bremen [32].

The rescue services serve the five districts Helmstedt, Gifhorn, Wolfsburg, Braunschweig, and Wolfenbüttel. In the catchment area of the rescue services, 10% of the population have a foreign citizenship. This percentage varies between 6.1% in Wolfenbüttel and 18.0% in the city of Salzgitter (own calculations) [33–35]. The 15 main countries of origin of registered foreigners within the serviced area of the rescue services involved in this study are – in decreasing order – Turkey, Syria, Poland, Italy, Rumania, China, Iraq, Kosovo, Russia, Serbia (without Kosovo), Bulgaria, Greece, Afghanistan, Spain, and Croatia [33]. Additionally, one-fifth of agricultural seasonal workers in Germany work in Lower Saxony [36], and 1.6 million foreign tourists travelled to Lower Saxony in 2017 [6].

The rescue service stations Wendhausen and Helmstedt are located close to the motorway A2, which is the most important east-west route in northern Germany, connecting The Netherlands with its significant harbours with Poland and other countries in the region of north-eastern Europe. Therefore, a relatively high number of sick or injured transit passengers, especially tourists and truck drivers are patients of these rescue stations [28, 30].. The rescue station in Braunschweig serves as a central reception centre of refugees and asylum seekers (the Zentrale Anlaufstelle für Asylbewerber (ZASt)). The rescue stations in Wendhausen, Königlutter, and Helmstedt serve in structurally weak and rural areas where the next emergency hospital care is often a substantially long distance away. The location close to a frequented motorway means that the problem of providing paramedic care for non-German-speaking patients appears to be much higher than in other comparable rural regions.

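### The DIVI free-text comparison is not tied to a within-station contrast, although documentation medium is fully determined by station and app use is not randomised

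*Protocol article*

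**What the plan says.** All references are to the Protocol article, section *Clinical trial* unless stated.

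- **Two media.** Under *Data collection*, at Wendhausen, Königslutter and Helmstedt "the DIVI-protocols are filled in using a laptop device". By contrast, "In Braunschweig the staff uses paper DIVI-protocols that will need to be digitalised". The paper forms are scanned, read by optical character recognition (OCR), and "will subsequently be reviewed to correct misrecognised values".
- **Free text as outcome.** Table 1 lists the description of the event, the history, the pre-medication and the working diagnosis as free text. *Data analysis of the clinical trial* says that change between control group 2 and the intervention group will be analysed "using paramedics’ feedback on questionnaires and comparing the content of the free text fields in the DIVI-protocols".
- **Tests.** Differences between groups "will be tested for statistical significance using Chi-squared or Mann-Whitney" *U* tests. No stratification by station or medium is stated. A separate sentence says the groups will also be compared by recruitment centre.
- **Matching.** The German-speaking comparison group is matched on age, sex, the medical condition and the emergency situation. Station is not on the list.
- **Who gets the app.** Under *Recruitment and informed consent*, use is left to the paramedics. Under *Drop-out criteria*, patients whose language the app lacks go to control group 2.
- **Different populations.** Under *Study site and study setting*, "The rescue station in Braunschweig serves as a central reception centre of refugees and asylum seekers", while Wendhausen and Helmstedt serve motorway transit traffic.

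**The concern.** When the outcome is how much information is recorded and how good it is, the recording route is part of the measurement. Crews may write more or less on a paper form than on a laptop, and scanning and OCR may lose some of it. Review of the OCR output can repair recognition errors but cannot restore what was never written.

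Only Braunschweig uses paper, so a group with more Braunschweig missions has more paper records. An unstratified test of free-text content then compares two groups that may have been measured by different mixtures of instruments. Two features make unequal mixtures plausible: crews decide whether to use the app, and the language list decides who can enter the intervention group. The main countries of origin in the catchment area include Romania, China, Bulgaria, Greece and Spain, whose main languages are not in Table 2. The patient mix also differs between the reception-centre station and the motorway stations.

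At stake is the DIVI part of the secondary outcome. A medium difference could appear as an app benefit or hide one. The comparison with German-speaking patients is exposed in the same way if matching ignores station.

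**Working it through.** The article gives no figure for a medium effect or for station shares by group, so there is no stated result to reproduce. The check sets out when bias arises and how large it could be under declared assumptions.

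**Inputs from the article (*Sample size estimation*, 2018 missions).** Wendhausen 1600, Königslutter 3500, Helmstedt 6200, Braunschweig 3500.

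- Total = 1600 + 3500 + 6200 + 3500 = 14,800.
- Braunschweig share = 3500 / 14,800 = 0.236.

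This is a share of all missions. Using it for foreign-language missions in control group 2 is an assumption.

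**Assumed inputs.** Let m be the amount, in within-station SD units, by which paper lowers the content score. Let p_C and p_I be the Braunschweig shares in control group 2 and the intervention group.

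**Step 1: bias with no app effect.** Bias (intervention minus control) = m × (p_C − p_I).

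- If p_C = p_I, the bias is 0 for every m.
- Gap of 10 points, m = 0.5: 0.10 × 0.5 = 0.05 SD.
- Gap of 20 points, m = 1: 0.20 × 1.0 = 0.20 SD.

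The sign follows which group has more paper. It reverses if paper yields more content than the laptop.

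**Step 2: variance with equal shares.** Factor = 1 + p(1 − p)m², with p = 0.236.

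- m = 0.5: 1 + 0.236 × 0.764 × 0.25 = 1.045.
- m = 1: 1 + 0.236 × 0.764 × 1 = 1.180.

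The standard error rises by √1.045 − 1 = 2% to √1.180 − 1 = 9%.

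**Step 3: false-positive rate of an unstratified two-sided 5% test.** This is a normal approximation for a mean difference (a stand-in for the rank test), with n per group, no app effect, p_C = 0.236 and m = 0.5:

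- SD = √(1 + m² × ½[p_C(1 − p_C) + p_I(1 − p_I)]) and SE = SD × √(2/n).
- Rate = 1 − Φ(1.96 − bias/SE) + Φ(−1.96 − bias/SE).

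| p_I | Bias (SD) | n = 75 | n = 150 | n = 300 |
|---|---|---|---|---|
| 0.10 | +0.07 | 7.0% | 9.0% | 13.0% |
| 0.236 | 0 | 5.0% | 5.0% | 5.0% |
| 0.35 | −0.06 | 6.3% | 7.7% | 10.4% |
| 0.50 | −0.13 | 12.3% | 19.9% | 34.9% |

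With m from 0.2 to 0.8, p_I from 0.10 to 0.50 and n from 50 to 300, the bias runs from −0.21 to +0.11 SD and the rate from 5% to 68%. The upper end needs the largest m, the largest gap and the largest n together.

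**Step 4: after stratification.** Within a station all records share one medium, so the between-station term drops out. Under the same assumptions the bias is 0 and the rate is 5%.

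**The case against.** The strongest reply is that the article already plans to compare groups by recruitment centre and sets its sample target with the aim of telling the four sites apart. Since only Braunschweig uses paper, a comparison by centre is also one by medium. This stands in part. But the centre sentence is separate from the free-text comparison and does not say that the app contrast is estimated within station or combined across stations.

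Second, the exact form of adjustment may sit in an analysis plan that is not shown. That is fair and limits the point to a recommendation. Still, the article itself names the tests and the matching variables, and neither includes station.

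Third, all stations can contribute to both groups, and Table 2 covers languages relevant to both settings, for example Arabic, Dari and Pashto as well as Polish, Lithuanian and Czech. This stands: different populations by station do not prove a different station mix by group.

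Three stronger readings are tempting, and the documents do not support them:

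- A reader might infer that the medium is already mixed into the app effect. That requires unequal Braunschweig shares, which are not given.
- A reader might infer that the Braunschweig forms are handwritten. The text says only that they are paper.
- A reader might infer that free text escapes the OCR review because the review concerns values. The article draws no such line.

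**Conclusion.** The point holds in a limited, conditional form. Medium is fully aliased with station, DIVI free text feeds the secondary outcome, and the article does not tie that comparison to a within-station estimate in a non-randomised design. A medium difference biases the app contrast only if the Braunschweig share differs between control group 2 and the intervention group. Otherwise it adds a modest amount of noise.

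The illustrative 0.05 to 0.20 SD rests wholly on assumed share gaps and medium effects, and its direction is unknown. Bias of that order would matter because the sample-size section aims to detect small effects. The primary outcome and the questionnaire part of the secondary outcome do not depend on the medium. This is a minor to moderate point, worth acting on because the remedy costs almost nothing.

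**What to change.** 1. Make a station-stratified comparison the main analysis of the DIVI-based secondary outcome: for example a van Elteren test for scores and Cochran-Mantel-Haenszel for categorical items. Report the Braunschweig share in each group beside it.
2. Add station to the matching variables for the German-speaking group wherever DIVI content is compared.
3. Digitise Braunschweig free text in the same way for every group being compared. Do not transcribe only the foreign-language forms by hand. That would make their measurement differ from that of German-speaking records at the same station, where the described route is now uniform.

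**Cost.** Station is already needed for the planned comparison by centre, so no new data are required. Precision falls slightly if some station strata are sparse, and matching becomes somewhat harder. If hand transcription were preferred, the foreign-language forms at Braunschweig would number about 0.236 × 400 to 0.236 × 600 = 95 to 142 a year, assuming a proportional share of the 400 to 600 patients the article hopes for. The matched German-speaking forms would have to be added to that.

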#### Recruitment and informed consent

Within the clinical trial, data are collected about two different parties. On the one hand, patients from whom medical and demographic data are collected, and on the other hand, paramedics, who express their perspective on the communication with patients, their asssessment of the app, and of whom data will be collected when they use the app. All these data will be collected anonymously. Whether paramedics use the app is exclusively their decision and responsibility. Clear rules will be put in place so that under no circumstances rescue personnel or patients are endangered because of use of the app. Using the app and participating in the study is voluntary. Paramedics need to declare written informed consent (see above).

No written consent is obtained from the patients because it can be assumed that their well-being is not endangered by the intervention. Obtaining informed consent is desirable, but under the circumstances of an emergency operation, we would meet insurmountable hurdles with obvious ethical conflicts. Adequate informed consent seems hardly possible with patients in extreme medical situations and who do not speak German. In addition, giving adequate information would prolong the time span of the rescue mission and delay transport and thereby endanger patients and paramedics alike. Obtaining an informed consent retrospectively is likewise associated with obstacles because study participants may come from abroad, and collecting contact details (telephone number, name, address) – and explaining why these are asked for – is equally difficult in an emergency situation (and some patients may not wish to give their contact details, e.g. due to their residence status). However, if a patient objects to communicating via the device, paramedics will abort the use. Only anonymised patient data are collected, and this is done in a way that effectively prevents retrospective identification.

#### Inclusion criteria for patients

Patients who meet the following criteria are eligible to participate in the study:
Control group 1: German-speaking patients of all ages who do not use the app.Control group 2: Non-German-speaking patients of all ages who do not use the app (i.e. within the first period of recruitment and because of drop-out in the second recruitment stage)Interventional group: Non-German-speaking patients of all ages who speak one of the available languages (cp. Table 2) and who are responsive to use the app.

**Table 2 Tab2:** Supported languages

• Arabic: possible dialects are Syrian Arabic, Egyptian Arabic, Moroccan Arabic (spelling Modern Standard Arabic) • Bosnian • Croatian • Czech • Dari • English • French	• Italian • Kurdish: possible dialects are Sorani and Kurmanji • Lithuanian • Pashto • Persian • Polish • Russian • Serbian • Turkish

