### Clinical trial

In order to evaluate the effect of the developed app, we will conduct a prospective open intervention study. The main purpose of the clinical trial is to assess how the use of the app affects the perceived quality of understanding of non-German-speaking patients from the paramedics’ point of view **(primary outcome)** and how it affects the quality and quantity of information obtained from patients with language barriers **(secondary outcome).** In addition, we will assess whether the tool is perceived as helpful and easy to handle in daily use by the paramedics.

For this purpose, two different patient control groups are recruited and compared with one interventional patient group. Control group 1 consists of German-speaking patients, whereas control group 2 consists of non-German-speaking patients with whom the communication tool is not used. The interventional group consists of non-German-speaking patients with whom paramedics use the tool to communicate with patients. German-speaking control group 1 serves as baseline for on-scene times, intubation rates, and requests for on-scene emergency doctor support. The recruitment period for this group will be at least 12 months because a very large total number of cases is necessary for the selection of matched control groups. By comparing data on control group 2 and on the interventional group, the immediate effect of the tool on communication and information gathering with non-German-speaking patients can be analysed.

As to the primary outcome, we expect that using the tool, paramedics perceive the communication with non-German-speaking patients as easier and more fruitful. Therefore, we will analyse paramedics’ feedback on questionnaires for each emergency drive with foreign-language patients concerning the communication and mutual understanding with patients (see below). Paramedics are asked to report their experience with the tool to assess its acceptance and usability (see above).

Moreover, this study attempts to generate first knowledge about the extent and relevance of language barriers in emergency operations. With regard to the secondary outcome (quality and quantity of information obtained from the patient), we will be able to compare non-German-speaking patients with German-speaking patients and take demographic and medical aspects into account.

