#### Drop-out criteria for patients from the interventional group

When the intervention takes place, paramedics can refuse to use the app at any time. They are not to use the app when it presumably places the patient or themselves at risk (e.g. rescue operation on a busy and unblocked motorway). Furthermore, the app is not to be used in emergencies with immediate action implications (e.g. cardiopulmonary resuscitation or transport to the hospital necessary without any delay) or if the patient has a severe limitation of consciousness. If patients do not speak languages provided in the app (cp. Table 2), they are excluded from the interventional group but serve as control patients in group 2. Patients who meet the eligibility criteria but with whom paramedics do not use the intervention will be analysed separately.

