## Discussion

While there have been a quite a number of studies on the medical care of refugees and migrants in recent years, the emergency service with foreign-language patients has not yet been the subject of scientific concern. However, there are indications that language barriers pose a particular challenge to rescue workers and might endanger patients [16, 17].

For the first time, this study attempts to generate knowledge about language barriers in medical emergency operations. Furthermore, we will develop and implement the digital communication tool together with the end-users in an action-oriented research approach with an interdisciplinary team. This implies that the paramedic staff of four participating emergency medical service stations is involved in the whole development and implementation process. This certainly complex approach ensures that the app and the hardware meet the needs of the end-users and increases the likelihood of long-term implementation even after the study is completed. The use of technical solutions to overcome language barrier seems logical: professional interpreters, which are gold standard, can by nature not be present at the emergency scene. Lay interpreters, who are often family members, are problematic both in terms of translation accuracy and confidentiality [38, 39].

The app is expected to facilitate communication with foreign-language patients in paramedic care. A comparison of data on non-German-speaking patients with and without the developed communication tool is intended to show whether the app improves the perceived quality of understanding (primary outcome) and the quality and quantity of information received from the patient (secondary outcome). We expect that paramedics who use the app will be able to obtain information about their patients that they could not collect otherwise. This may lead to a better and safer provision of paramedic care.

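### First-period controls enter whatever other communication aid was at hand, while app patients are chosen by crews, so the unadjusted primary contrast can mix the tool's effect with access to an interpreter or a shared language

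*Protocol article*

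**What the plan says.** Under *Inclusion criteria for patients* the comparator is "Control group 2: Non-German-speaking patients of all ages who do not use the app", reached by two routes: "i.e. within the first period of recruitment and because of drop-out in the second recruitment stage". The interventional group is "Non-German-speaking patients of all ages who speak one of the available languages (cp. Table 2) and who are responsive to use the app". Neither definition mentions another means of communication.

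*Recruitment and informed consent* leaves use to the crew: "Whether paramedics use the app is exclusively their decision and responsibility". *Drop-out criteria for patients from the interventional group* says of patients whose language the app lacks that "they are excluded from the interventional group but serve as control patients in group 2". It then says: "Patients who meet the eligibility criteria but with whom paramedics do not use the intervention will be analysed separately".

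The *Clinical trial* section expects that, from control group 2 against the interventional group, "the immediate effect of the tool on communication and information gathering with non-German-speaking patients can be analysed". For group differences, *Data analysis of the clinical trial* names Chi-squared and Mann-Whitney tests. It describes matching only for the comparison with German-speaking patients. The *Discussion* acknowledges an existing alternative to the app: "Lay interpreters, who are often family members, are problematic both in terms of translation accuracy and confidentiality".

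**The concern.** The primary outcome is how well the crew felt it understood the patient. An interpreting relative or a shared third language acts on that rating directly. English and French are among the supported languages, so a patient whom the crew can already address in English counts as an ordinary first-period control.

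First-period controls are not selected on whether the crew needed help to communicate, whereas app patients are selected by crews using a tool built to overcome a barrier. If crews open it less often when another aid is at hand, control group 2 holds proportionally more aided missions and its ratings rise for a reason unrelated to the app. The unadjusted contrast would then understate what the app does.

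**Working it through.** **1. Where each kind of mission goes**

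| Mission with a non-German-speaking patient | First period | Second period |
|---|---|---|
| Supported language, responsive, no other aid | Control group 2 | Interventional if the app is used; otherwise control group 2 as a drop-out (inclusion criteria) or separate analysis (drop-out criteria) |
| Supported language, responsive, aid available | Control group 2 | Same routes; app use less likely (inference) |
| Unsupported language | Control group 2 | Control group 2 |
| Not responsive | Control group 2 | Not interventional; control group 2 if counted as a drop-out |

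The second row carries the point. On either reading of the second-period rules, aided first-period missions stay in the control group. Aided second-period missions without the app either join them or leave the contrast. Restricting controls to supported-language, responsive patients would not remove the difference, because aided patients can meet both conditions.

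**2. The plan's own figures**

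The article gives no rate for this factor. Its sample-size figures reproduce: 1200 × 108/1000 = 129.6, stated as 130 cases a year; 4 sites × 50 to 75 = 200 to 300 patients.

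**3. Illustration on proportions (all rates assumed)**

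- Good understanding in 40% of unaided and 70% of aided missions.
- Aid available in a share q0 of control group 2 and q1 = 10% of app missions.
- Control rate = 0.70·q0 + 0.40·(1 − q0).
- App with no effect: 0.70 × 0.10 + 0.40 × 0.90 = 0.43.
- App adding 20 points in unaided missions only: 0.70 × 0.10 + 0.60 × 0.90 = 0.61.

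| q0 | Control rate | Difference, no app effect | Difference, true +20 points in unaided missions |
|---|---|---|---|
| 10% | 0.43 | 0 | +18 points |
| 15% | 0.445 | −1.5 | +16.5 |
| 30% | 0.49 | −6 | +12 |
| 40% | 0.52 | −9 | +9 |
| 50% | 0.55 | −12 | +6 |

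The distortion is 0.30 × (q0 − q1). The step from 20 to 18 points in the first row is not bias: it arises because the assumed app adds nothing in aided missions.

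**4. Illustration on a rating scale (assumed)**

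Take a true effect of d = 0.5 SD where no aid exists, a share f of controls aided and rated equal to the app, and no aided app missions. The observed effect is (1 − f)·d and the control variance is 1 + f(1 − f)·d². Power is Φ(effect/SE − 1.96), with SE = √[(1 + control variance)/n], two-sided 0.05. The article's 50 to 75 is taken as the size of each group.

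| f | Observed effect | Power, n = 50 | Power, n = 75 |
|---|---|---|---|
| 0 | 0.50 SD | 0.71 | 0.87 |
| 0.2 | 0.40 SD | 0.51 | 0.68 |
| 0.3 | 0.35 SD | 0.41 | 0.56 |

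**5. The opposing channel**

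Suppose, as an extreme, that a share r of control missions involved patients unable to respond and that none of these was rated good. The control rate in step 3 becomes (1 − r) times its value. With no app effect, the two channels cancel when r = 0.015/0.445 = 3.4% (q0 = 15%), 0.06/0.49 = 12% (q0 = 30%) or 0.12/0.55 = 22% (q0 = 50%). Above those shares the contrast would favour the app. The direction of the total bias cannot be read from the document.

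**The case against.** **The comparator is legitimate.** A reader might infer that the trial promised a comparison with an unbridged barrier and broke that promise. It did not: the article compares non-German-speaking patients with and without the tool, and usual practice with whatever help is at hand is a fair comparator. What stands is narrower: such a comparison needs similar selection in both groups, and only one is chosen by crews.

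**Control group 2 is not defined by non-use alone.** Language, period, drop-out route and unsupported language also count, and the drop-out section sets aside eligible second-period non-users. So one cannot say that all aided second-period missions without the app fall into control group 2. The clear case is the first period.

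**Less use of the app in aided missions is not stated.** Both app modes can address relatives and other third parties, so a relative's presence does not rule out use. This weakens the likely size of the selection, not the possibility of it.

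**The shares may be small.** The Background says on-site interpretation is mostly very limited in emergency care, which does not favour 30% to 50%. It says nothing of crews and patients sharing a third language.

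**The information may already be collected.** Table 1 has no such field, but it lists rescue-protocol data, and the article says that protocol does not cover communication. The questionnaire does, and its content is in Additional file 1, which is not shown. Absence of the item cannot be asserted. Covariate detail may also sit in an unseen analysis plan; what the article states is a causal reading of this contrast and unadjusted tests.

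**Conclusion.** The point holds in limited form. As the groups are defined, availability of an interpreter or shared language may differ between control group 2 and the interventional group, and the stated tests cannot separate that from the tool's effect. This channel would tend to understate the app. Under the assumed rates it is worth nothing if the shares are equal, 1.5 points at 15% against 10%, and 6 to 12 points at 30% to 50% against 10%. None of these shares comes from the document.

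A reader might go further and infer that the trial is biased against the app overall. The document does not support that: control group 2 has no responsiveness condition, which may push the other way, and the net direction is undetermined. The change is worth making because it is cheap and bears on the primary outcome; the point does not invalidate the design.

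**What to change.** 1. **Questionnaire, both periods.** Use, or if Additional file 1 lacks it add, one item: on arrival, was an interpreting person available, a shared third language, both, or neither? It must refer to the time before app use and be answered whether or not the app was used. An item asking what actually carried the communication would not do. The app can change that answer, so like missions would be kept in one group and removed from the other.
2. **Data analysis section.** Stratify or adjust the comparison of perceived understanding between the interventional group and control group 2 by this item. Report the stratum with no aid available as the estimate of the tool's effect where no other aid exists, and show the aid-available stratum separately.
3. **Group definitions.** Reconcile the inclusion criteria, which admit second-period drop-outs to control group 2, with the drop-out section, which analyses eligible non-users separately.

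**Cost.** One form item at most, some wording, and less precision within strata. With 30% of controls and 10% of app missions aided (assumed), groups of 50 to 75 would leave 0.70 × 50 = 35 to 0.70 × 75 ≈ 52 controls and 0.90 × 50 = 45 to 0.90 × 75 ≈ 67 app missions in the no-aid stratum. The item deals only with this factor; other reasons for which crews choose to use the app remain.
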